#### Analysis of MDRO-related hospital costs

A further study will assess the costs of MDRO management in hospitalized patients. The analysis is based on the data from the documentation sheet on the progression of MDRO status, and from the documentation sheet for nursing efforts. Additionally, lengths of hospital stay and other parameters relating to the German Diagnosis Related Group payment system will be evaluated with a focus on remuneration effects. MDRO-positive patients will be compared with MDRO-negative patients (separately for each pathogen) via matching analysis (ratio 1:3). Matching variables are the main discharge diagnosis (ICD-10) and the type of discharging ward.

### Follow-up examinations

A six-month follow-up program is planned for patients taking part in the study and who have been screened for MDRO during their hospital stay. This program is divided into three parts:Health-related quality of life: quality of life survey six months after discharge from hospital, in comparison to patients who were tested negative for MDRO during their time as in-patient (control group). To this end, the modified SF-36 form will be sent by mail to the home addresses by the independent trust agency including a return mail envelope addressed to the trust agency.Sustainability of MRSA decolonization: MRSA status will be determined by culture diagnosis six months after discharge from hospital. For this test, a trained nurse will visit the patient at home and take a nasal and, if requested, throat and/or wound swab. The sample will be sent to a central laboratory.Health care utilization over a period of six months after discharge for patients who were screened for MDRO during their hospital stay. The data for positive patients are compared to those with negative results. For this reason, a patient-reported questionnaire including a reply-paid envelope will be sent to the home address by the independent trust agency. Secondary data of health insurance companies will be analyzed as well.

In each case, the accompanying informed consent policies have to be agreed by the patient.

### Methods of data collection and variables

Baseline data collection conducted with participating hospitals included a questionnaire to assess structural parameters (e.g. number of beds/cases/single rooms, staffing ratio, staff level of qualification, prevalence of advanced training in hygiene), and process parameters (procedures of registering, documentation and reporting of MDROs). At the end of each study phase (Fig. 2), potential changes in structural or process parameters were documented, together with use of antibiotics and disinfectants for the given period.Data on the use of antibiotics and disinfectants over the three years prior to this study, as well as test utilization and resulting positive MDRO rates, were documented by the study team.The level of knowledge of the nursing staff and physicians on MDROs was assessed by a multiple choice test at the beginning of the instructional courses.Structured questionnaires and documentation forms were used during the intervention period, and, for the delayed-intervention group only, during the observation period, identical for all hospitals (Table 3).

**Table 3 Tab3:** Documents used for data acquisition during the intervention and observation phase

Documents used in the intervention and observation phase	Description of data collected	Document to be filled out by
Patient admission sheet	Risk factors for MDRO colonization or infection	Health care workers during anamnesis, or, alternatively, by the patient (with help of staff)
Documentation sheet on the progression of MDRO status including transition section^**a**^ for the physician responsible for subsequent treatment	Admission and discharge data, sample taking and diagnosis, where applicable isolation measures, control swab test, time of infection, information for physician responsible for subsequent treatment	Health care workers
Documentation sheet for nursing efforts for MDRO^b^ infections/colonizations	Nursing workload in minutes	Nursing staff
Patient evaluation sheet	Subjective evaluation of hygiene measures in the hospital	Patient
Quality of life questionnaire (modified version of the SF-36)	Health-related quality of life in the last seven days	Patient

^**a**^This form differs slightly for the delayed intervention group and the immediate intervention group. In order to exert as little influence as possible on the documentation of previous hygiene management programs, the form for the delayed intervention group does not include the transition section for the physician responsible for subsequent treatment

^b^also relevant for reimbursement by the statutory health insurance

Note: Documents can be downloaded from: http://www2.medizin.uni-greifswald.de/icm/index.php?id=hicare

The usage of the questionnaires for the collection of patient data is shown in the flow chart in Fig. 3. Participation was only requested if the patient was expected to remain in the ward for at least 48 hours. The patient admission sheet and both MDRO documentation sheets were designed to replace the previous documentation used by the hospitals. This measure also avoids time and effort of double documentation. The treatment sheets are designed such that the original has space for a label with the patient’s identification and is included in the patient’s file as treatment documentation after the patient is discharged. For the sake of data privacy protection, the carbon copy that is used for our concomitant research will not have a label with patient identifying data. Both the original and the carbon copy are provided with a document barcode, allowing a mapping of multiple documents to a single pseudonym and preserving anonymity for non-consenters.

**Fig. 3 Fig3:**
[figure not shown]
Patient-specific study workflow — intervention group

A workflow-oriented documentation system was developed that is made available to the participating wards on a tablet PC, a *Medical Clinical Assistant* (MCA) with an integrated barcode scanner and a touch screen that can be disinfected. This system serves two purposes:i.Support during the studyUpon admission of a patient who is expected to spend at least 48 hours on the ward, the basic data (given name, surname, and date of birth) are entered into the system. The system then guides the staff through the sequence required by the study according to the individual patient, indicating which forms are to be filled out at which time. After completion, the forms respectively their copies are dropped into a special mailbox and are subsequently transferred to a central data management. Patient permissions are collected in a separate container and are transferred to the independent trust agent. Staff members from the participating wards are trained in how to use the documentation system by HARMONIC study personnel.ii.Data privacy protectionPatient data entered into the workflow-oriented documentation system are encrypted by hospital-specific private keys and only visible to the responsible HCWs. To allow the individual forms and copies to be correlated to a specific person, each sheet of the form contains an ID that can be read out by the barcode scanner integrated in the MCA. This system provides the relational mapping of the individual sheet IDs to the participant ID, while assuring the data privacy protection.

### Data management and protection procedures

#### Monitoring procedures

The workflow-oriented documentation system was developed as a web-based solution. This allows real-time monitoring of the individual paper forms, so that any problem arising with the use of the forms can be quickly detected and solved. The monitoring dashboard contains aggregated data on the usage of the forms, but does not show any data about individuals.

#### Data protection procedures

A data protection plan was developed for the HARMONIC study in conjunction with the State Commissioner for Data Protection and Freedom of Information. If a patient gives permission to store his or her treatment data under a pseudonym, the personal identifying data (name, address) is collected on the informed consent document. Management of the consent documents is performed by an independent trust agent. Pseudonymized medical data are stored in a research database separated from the identifying data in an approach (Fig. 4) that follows the recommendations of the “Generic solutions for data protection in medical research networks – model B”, developed by the umbrella organization for networked medical research in Germany (TMF) [30, 31]. These recommendations were accepted by the German conference of federal and state data protection commissioners.

**Fig. 4 Fig4:**
[figure not shown]
Data management activities and responsibilities

The study data originate from primary and secondary data sources and are registered using document IDs, serving as study pseudonyms. Identifying data and medical data are processed as shown in Fig. 4. In the research database, only double pseudonymized data are stored, which prevents re-identification of the patient while analyzing the data. If necessary, further measures will be taken to impede re-identification, e.g. aggregation or precision reduction of informative variables such as age.

If no informed consent can be obtained, no identifying data will be transmitted. In these cases, a follow-up is not possible.

### Data analysis

#### Sample size

According to German screening recommendations on MRSA, about 40 % of patients admitted in acute hospitals in Germany have risk factors for MRSA [32]. It has been shown that screening recommendations are not followed completely, despite their obligatory character [33]. Based on information solicited with our institutional questionnaire, not all of the participating hospitals had fully adapted to the recommendations at baseline. Thus, as basis for sample size calculations, our intervention was assumed to improve the screening rate in MRSA risk patients from 60 % (control group) to 90 % (intervention group). The expected sample of > 1000 patients in each group results in a very high statistical power (approaching 1.0) for this study (type-I risk: 0.05).

With an observation period of six months for each of the 24 participating wards, at least 5,000 patient admissions with an anticipated stay over 48 hours are expected. Based on previous examinations [7, 8, 34, 35], an MRSA prevalence at admission of approximately 1 to 3 % is anticipated. Accordingly, 50 to 150 MRSA positive patients would be eligible for follow-up examinations.

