## Methods and design

### Design overview and setting

A total of 12 hospitals providing acute care participate in the HICARE project. Due to lack of personnel and time resources, four of these hospitals could not participate in the HARMONIC study. Therefore, the study was conducted in eight hospitals in the Health Region Baltic Sea Coast in Germany (Fig. 1). The study was designed as an 18-month prospective intervention study, which aims at implementing a multimodal hygiene management program. The recruitment of study hospitals started right after ethics approval (29th of May 2012). Hospitals were randomized concerning the immediate implementation of the intervention program *versus* the campaign starting with a six-month delay, in four strata of two hospitals each. The strata were defined by level of care (maximum care *versus* standard care) and hospital size (>25,000; 10,000 to 25,000; 5,000 to 10,000; and < 5,000 annual discharges). Table 1 shows the characteristics used to match the participating hospitals in according pairs. The hospitals in the delayed-intervention group received the intervention measures after completion of the first phase of the study (Fig. 2). Data collection started in February 2013 and was finished for the main study in November 2014. Analysis will be finished in June 2015 and December 2015 for two of the nested studies.

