#### Data analysis

To evaluate the effect of the outcome measures, a hierarchical logistic regression model for the log-odds of a patient’s chance to be screened for either MRSA, VRE, or MRGN was formulated as follows:

(level 1):$$ \mathrm{logit}{\left( antibiogram=1\right)}_{ij}={a}_j+{\beta}_1{X}_{1ij}+{\beta}_2{X}_{2ij}+\cdots +{\varepsilon}_{ij} $$

with$$ \begin{array}{l}\mathrm{i}:=1\kern0.28em \mathrm{t}\mathrm{o}\kern0.28em \mathrm{k}\kern4.5em \mathrm{patient}\kern.3em \mathrm{i}\mathrm{ndex}\kern1em \\ {}\mathrm{j}:=1\kern0.28em \mathrm{t}\mathrm{o}\kern0.24em 8\kern4.5em \mathrm{ID}\kern.3em \mathrm{number}\kern0.28em \mathrm{o}\mathrm{f}\kern0.28em \mathrm{hospital}\kern1em \\ {}{\mathrm{X}}_1\kern0.28em \mathrm{t}\mathrm{o}\kern0.28em {\mathrm{X}}_{\mathrm{m}}\kern4.8em \mathrm{i}\mathrm{ndividual}\kern.3em \mathrm{patient}\kern0.28em \mathrm{c}\mathrm{hartacteristics},\mathrm{such}\kern.2em \mathrm{a}\mathrm{s}\kern.2em \mathrm{a}\mathrm{ge},\mathrm{sex},\kern.2em \mathrm{s}\mathrm{urgical}\kern0.28em \mathrm{t}\mathrm{reatment}\kern.2em \mathrm{e}\mathrm{t}\mathrm{c}.\kern1em \end{array} $$

As the intervention program was implemented on the level of participating hospitals, the following level-2 equation (random intercept model) was a priori specified for statistical analysis:$$ {a}_j={\gamma}_{00}+{\gamma}_{01}{\zeta}_{1j}+{\gamma}_{02}{\zeta}_{2j}+\cdots +{\omega}_j $$

with γ_00_ representing the global base rate parameter for screening tests, and γ_0j_ hospital-specific additions depending on the intervention group (ζ_1_ = 1 for intervention period, 0 otherwise), hospital capacity (ζ_2j_ measured on metric scale level) or similar. To test the main hypothesis, the significance of parameter γ_01_ (deviation from zero) will be tested. Control for potential center effects is exerted by introduction of the ω_j_ center-specific error terms of the intercept parameter.

It will be decided during the model selection process whether or not other variables on the hospital level are to be introduced in separate level-2 equations as so-called random slope-effects (e.g. hospital-specific tendencies towards testing older patients more frequently).

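### The stated power treats more than 2,000 patients as independent although eight hospitals in four pairs are randomised; it is unsupported, and overstated unless the between-hospital ICC is very small

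*Protocol article*

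**What the plan says.** All references are to the protocol article.

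- **Sample size:** the assumed improvement in the MRSA screening rate among risk patients is from 60% (control) to 90% (intervention). "The expected sample of > 1000 patients in each group" then "results in a very high statistical power (approaching 1.0) for this study" ("type-I risk: 0.05"). No ICC, design effect, hospital count or between-hospital variance enters this statement.
- **Design overview and setting:** hospitals were randomised to immediate or six-month-delayed implementation, "in four strata of two hospitals each". That is four hospitals per group.
- **Data analysis:** "As the intervention program was implemented on the level of participating hospitals", the intervention term sits in the level-2 (hospital) equation of a random-intercept logistic model. "To test the main hypothesis, the significance of parameter γ_01_ (deviation from zero) will be tested".
- **Sample size**, on baseline practice: "not all of the participating hospitals had fully adapted to the recommendations at baseline". **Strengths and limitations** adds that some control hospitals are presumed to follow the national recommendations already, and that the extent may differ.

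**The concern.** The power statement uses one unit and the rest of the design another. Power is counted in patients, whereas randomisation and the main test operate on hospitals. With four hospitals per group, variation between hospitals sets a floor on the standard error that more patients cannot lower.

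Screening at admission is largely a matter of hospital practice, and the article itself says that hospitals differed in adopting the recommendations. A near-zero ICC is therefore hard to take for granted.

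At stake is how the primary outcome is interpreted. The Implications section says the results will indicate whether the regimen is worth continuing. If power is described as virtually certain, a non-significant result invites the reading that the intervention does not work, when the trial might simply have been unable to tell.

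**Working it through.** **Inputs**

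- 60% against 90%, 1,000 patients per group and alpha 0.05: Sample size section.
- Two-sided: not stated there; taken from the test of deviation from zero in the Data analysis section.
- Four hospitals per group: eight hospitals randomised in four pairs, Design overview and setting.
- 1,000 / 4 = 250 risk patients per hospital. Equal numbers are an assumption.
- ICC: not in the document. A range of 0.02 to 0.30 is assumed.

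**Step 1: reproduce the stated figure.** With independent patients, SE = √(0.60×0.40/1000 + 0.90×0.10/1000) = √(0.33/1000) = 0.0182, and 0.30/0.0182 = 16.5. Power is 1.000. The stated figure therefore reproduces from patient-level inputs alone. On that basis about 99 patients per group would already give 99.9%.

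**Step 2: make the hospital the unit.**

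- Design effect: DE = 1 + (250 − 1) × ICC.
- SE = √(0.33 × DE / 1000).
- Noncentrality = 0.30 / SE.
- Power from the noncentral t: 6 df (critical value 2.447) for an unmatched 4 against 4 comparison, or 3 df (critical value 3.182) for four pairs with no gain from matching.

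Worked line for ICC 0.10: DE = 25.9; SE = √(0.33 × 25.9/1000) = 0.0924; noncentrality 3.25; power 0.77 on 6 df and 0.59 on 3 df.

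The SD column is √(ICC × 0.24), the spread of true rates among control hospitals that each ICC implies. The last column repeats the calculation for 60% against 75%, with 0.24 + 0.1875 = 0.4275 replacing 0.33 and 0.15 replacing 0.30.

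| ICC | SD, control hospitals | DE | Effective n per group | Power, 60% v 90%: 6 df (3 df) | Power, 60% v 75%: 6 df |
|---|---|---|---|---|---|
| 0.02 | 7 points | 6.0 | 167 | 1.00 (0.99) | 0.70 |
| 0.05 | 11 points | 13.5 | 74 | 0.96 (0.84) | 0.38 |
| 0.10 | 15 points | 25.9 | 39 | 0.77 (0.59) | 0.23 |
| 0.20 | 22 points | 50.8 | 20 | 0.49 (0.36) | 0.14 |
| 0.30 | 27 points | 75.7 | 13 | 0.36 (0.27) | 0.11 |

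A simulation with beta-distributed hospital rates (20,000 runs) agrees for the 30-point effect: 0.95 (0.84) at ICC 0.05 and 0.77 (0.60) at ICC 0.10.

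**Step 3: where the claim stops holding.** Power for the 30-point effect drops below 0.98 once the ICC exceeds about 0.042 (6 df) or 0.023 (3 df), and below 0.80 once it exceeds about 0.093 or 0.057.

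**Step 4: does the patient count matter?** With unlimited patients per hospital, SE tends to √(0.33 × ICC / 4). At ICC 0.10 this is 0.0908, and 6-df power is about 0.79 against 0.77 with 250 patients. The number of hospitals, not of patients, is the limit.

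**Step 5: a sense of scale (hypothetical).** Suppose one control hospital in four is already at 90% and the group mean is 60%. The other three are then at 50%, since (0.90 + 3 × 0.50)/4 = 0.60. The variance of the four rates is 0.12/4 = 0.03 or 0.12/3 = 0.04, depending on the divisor. Dividing by 0.24 gives an ICC of about 0.13 to 0.17. The article does not report such a split; the example only shows that modest unevenness in adoption takes the ICC well past 0.04.

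**The case against.** **The figure is not disproved.** The article gives no ICC. At about 0.02 with equal hospital sizes, power really is 0.99 to 1.00, because 60% against 90% is a large effect. A reader might infer that the design certainly lacks the stated power, or has only an even chance of success. The documents do not support that: a power near one half on 6 df needs an ICC of about 0.20, which nothing in the text establishes. This stands.

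**The article does not describe a large spread.** It says that some hospitals had not fully adapted and that extent may differ. That makes a near-zero ICC hard to assume but gives no size. This stands.

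**Within-hospital information may help.** The model codes the intervention term by intervention period, and patients were monitored in each study phase, so delayed hospitals can supply both control and intervention data. As an illustration, take only the four delayed hospitals, 250 patients per period, a correlation of 0.8 between a hospital's two rates, no time trend and a paired t on 3 df. The variance of the mean change is [σ₁² + σ₂² − 2(0.8)σ₁σ₂ + (1 − ICC)(0.33)/250]/4, with σ₁² = 0.24 × ICC and σ₂² = 0.09 × ICC. Power is then above 0.99 at ICC 0.05, 0.96 at 0.10 and 0.80 at 0.20. This stands in part. However, the Sample size section powers control group against intervention group, the displayed model has no period term, and the Background gives changes over time as the reason for having a control group.

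**Unequal hospital size.** It is tempting to argue further loss from the 4,000 to 40,000 annual discharges in Table 1. Patients come from comparable subsets of three wards per hospital, so total discharges are a poor guide to enrolled numbers. No figure is put on this here.

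**The analysis does account for clustering.** The planned model has a hospital random intercept. A reader might infer that the primary test ignores clustering; it does not. The fault is confined to the power statement.

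**Conclusion.** The concern holds in a conditional form. The arithmetic behind the stated power is correct for independent patients, but independence contradicts the article's own randomisation unit and analysis model. The figure is therefore unsupported as written.

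How far it is overstated depends on an ICC that the article does not give: not at all in practice near 0.02, to 0.77 (0.59) at 0.10 and 0.49 (0.36) at 0.20. These values rest on 250 risk patients in each of four hospitals per group, two-sided 5% and a parallel comparison. They would change if before-and-after data from the delayed hospitals legitimately entered the contrast. For an effect half as large, 6-df power is already only 0.70 at ICC 0.02.

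**What to change.** In the Sample size section:

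1. Delete the claim that power approaches 1.0.
2. Restate power from eight hospitals in four pairs, with small-sample degrees of freedom, as a table over an ICC range that includes 0.02 (for example 0.02 to 0.30), for the 30-point effect and a smaller one. Give the reason for whichever ICC is thought most plausible.
3. Say whether the delayed hospitals' intervention-phase data enter the powered contrast and, if so, what is assumed about time trends.
4. State that the number of hospitals limits power, and that a non-significant result is to be read from its confidence interval.

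If unequal cluster size is addressed, use enrolled or expected ward-level numbers, not total discharges.

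The cost is some wording and one table. No extra patients and no change to the design or model are needed, which matters because data collection has finished. The downside is that the stated power becomes less favourable.

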#### Data analysis

To evaluate the effect of the outcome measures, a hierarchical logistic regression model for the log-odds of a patient’s chance to be screened for either MRSA, VRE, or MRGN was formulated as follows:

(level 1):$$ \mathrm{logit}{\left( antibiogram=1\right)}_{ij}={a}_j+{\beta}_1{X}_{1ij}+{\beta}_2{X}_{2ij}+\cdots +{\varepsilon}_{ij} $$

with$$ \begin{array}{l}\mathrm{i}:=1\kern0.28em \mathrm{t}\mathrm{o}\kern0.28em \mathrm{k}\kern4.5em \mathrm{patient}\kern.3em \mathrm{i}\mathrm{ndex}\kern1em \\ {}\mathrm{j}:=1\kern0.28em \mathrm{t}\mathrm{o}\kern0.24em 8\kern4.5em \mathrm{ID}\kern.3em \mathrm{number}\kern0.28em \mathrm{o}\mathrm{f}\kern0.28em \mathrm{hospital}\kern1em \\ {}{\mathrm{X}}_1\kern0.28em \mathrm{t}\mathrm{o}\kern0.28em {\mathrm{X}}_{\mathrm{m}}\kern4.8em \mathrm{i}\mathrm{ndividual}\kern.3em \mathrm{patient}\kern0.28em \mathrm{c}\mathrm{hartacteristics},\mathrm{such}\kern.2em \mathrm{a}\mathrm{s}\kern.2em \mathrm{a}\mathrm{ge},\mathrm{sex},\kern.2em \mathrm{s}\mathrm{urgical}\kern0.28em \mathrm{t}\mathrm{reatment}\kern.2em \mathrm{e}\mathrm{t}\mathrm{c}.\kern1em \end{array} $$

As the intervention program was implemented on the level of participating hospitals, the following level-2 equation (random intercept model) was a priori specified for statistical analysis:$$ {a}_j={\gamma}_{00}+{\gamma}_{01}{\zeta}_{1j}+{\gamma}_{02}{\zeta}_{2j}+\cdots +{\omega}_j $$

with γ_00_ representing the global base rate parameter for screening tests, and γ_0j_ hospital-specific additions depending on the intervention group (ζ_1_ = 1 for intervention period, 0 otherwise), hospital capacity (ζ_2j_ measured on metric scale level) or similar. To test the main hypothesis, the significance of parameter γ_01_ (deviation from zero) will be tested. Control for potential center effects is exerted by introduction of the ω_j_ center-specific error terms of the intercept parameter.

It will be decided during the model selection process whether or not other variables on the hospital level are to be introduced in separate level-2 equations as so-called random slope-effects (e.g. hospital-specific tendencies towards testing older patients more frequently).

For an assessment of the differences between the matched groups in the costs of MDRO management and treatment, as well as in health-related quality of life, *t*-tests will be applied. In order to control for the influence of covariates, likewise multivariate analysis methods and, in particular, logistic regression analysis will be applied to address selected issues.

